### Blinding

2.11

Research participants, group researchers, and individuals who assess the outcomes will not have access to the details of group assignments. This ensures that bias for or against the tested treatment is unlikely to occur.

### Data management

2.12

Initially, an experienced team member ([name]) will be trained to collect data according to the study protocol. The qualification of the researcher is essential to ensure the quality of clinical trials. Data collection will be carried out through the REDCap website. Data management included baseline characteristics (demography, lifestyle, comorbidities, history of HPV treatment, history of long-term use of oral contraceptives, tumor characteristics, International Federation of Gynaecology and Obstetrics staging, and inclusion and exclusion criteria), potential confounds, and outcomes as per the QOL questionnaire. Participants who withdraw from our study will be followed up with, and data will be analyzed according to the intention-to-treat principle. All randomized participants will be followed up with for 2 months after randomization.

### Data extraction and statistical analysis

2.13

For the analysis of quantitative data, repeated measures ANOVA based on the linear mixed effects model will be used. A binary variable will also be created to indicate the occurrence of nausea in the 24 hours after the infusion in at least 1 of the 6 weeks. In this case, a logistic regression model will be used and the odds ratio of occurrence of nausea will be calculated for the 3 groups. Data presented in the text and tables will be reported as means and SDs, mean, absolute values and percentages (%). Statistical significance will be set at *P* <.05. The software that will be used is the R Project for Statistical Computing for Windows, VR version 4.0.2.

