#### Primary outcome

2.6.1

Seven relevant time points will be considered for evaluating the results based on the chemotherapy protocol of cisplatin with radiotherapy: baseline (P0), 7 days after the first dose of medication (P1), on every consecutive 7th day during a break in treatment (P2, P3, P4, P5, and P6), and 15 days after the last dose (P7).

The primary outcome includes controlling nausea and vomiting as evaluated using the Common Terminology Criteria for Adverse Events or CTCAE (gastrointestinal disorders-nausea/vomiting).^[21]^ The CTCAE for nausea (a disorder characterized by a queasy sensation and/or the urge to vomit) will be classified as Grade 1 (loss of appetite without alteration in eating habits), Grade 2 (oral intake decreased without significant weight loss, dehydration, or malnutrition), or Grade 3 (inadequate oral caloric or fluid intake; tube feeding, parenteral nutrition, or hospitalization indicated). Vomiting (a disorder characterized by the reflexive act of ejecting the stomach contents through the mouth) will be classified as Grade 1 (intervention not indicated), Grade 2 (outpatient IV hydration: medical intervention indicated), Grade 3 (tube feeding, parenteral nutrition, or hospitalization indicated), Grade 4 (life-threatening consequences), or Grade 5 (death) (Table 1).

**Table 1 T1:** Outcome measurements.

Outcome measurement	Explanation	Time points for assessment
CTCAE	Common terminology criteria for adverse events	T1, T2, T3, T4, T5, and T6
EORTC QLQ C30	European Organization for Research and Treatment of Cancer Quality of Life Questionnaire Core 30	T1, T2, T3, T4, T5, and T6
EORTC QLQ Cx24	EORTC quality of life cervical cancer module	T1, T2, T3, T4, T5, and T6
MGT	Morisky-Green Test to evaluate medication adherence	T1, T2, T3, T4, T5, and T6

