### Sample size

2.9

The sample size calculation will be established using G Power Software version 3.1.9.2 (https://www.psychologie.hhu.de/arbeitsgruppen/allgemeine-psychologie-und-arbeitspsychologie/gpower), considering a Cohen effect size of 0.40, a test power of 0.80, and a significance level of 5% (*P* value <.05).^[26]^ The sample is estimated to be of 39 patients with a potential addition of 20%, totaling 48 participants, which will be equally allocated (1:1:1) into 3 groups of 16 patients each (the ginger capsules 250 mg group, ginger capsules 500 gm group, and placebo group).

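### The protocol lists baseline (P0) as an evaluation time point but does not say how the mixed model uses it; making P0 a covariate rather than a response level is at least as precise

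*Protocol article*

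**What the plan says.** Section 2.6.1 (Primary outcome) sets out the time points for evaluating the results, starting with "baseline (P0), 7 days after the first dose of medication (P1" and running weekly to P6, then to P7 at 15 days after the last dose. Table 1, in the same section, schedules CTCAE, QLQ-C30, QLQ-CX24 and the adherence test at T1 to T6 only, with no T0.

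Section 2.13 (Data extraction and statistical analysis) names the model for quantitative data: "repeated measures ANOVA based on the linear mixed effects model will be used". For the binary nausea outcome, "a logistic regression model will be used and the odds ratio of occurrence of nausea will be calculated for the 3 groups". It gives no model terms for either. It does not mention baseline, and it does not say that the analyses are unadjusted.

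Section 2.12 (Data management) says that the collected data include "potential confounds, and outcomes as per the QOL questionnaire", without linking them to a model. Section 2.10 describes block randomisation 1:1:1 and names no stratification factor. Section 2.9 plans 16 patients per arm.

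**The concern.** A baseline score can enter a longitudinal model as a covariate or as one of the repeated responses. Section 2.6.1 puts P0 in the list of evaluation time points and section 2.13 calls the analysis a repeated measures ANOVA. A reader who combines the two would naturally make P0 a response level.

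That choice costs precision in either of the two usual tests. The group main effect averages in a visit at which no treatment effect can exist. The change-from-P0 contrast subtracts a single noisy measurement. With 16 patients per arm, and 13 if only the planned 39 are evaluable (39/3), the loss can be material for outcomes on which patients already differ before the first cisplatin dose. The quality-of-life scales are the likely case.

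**Working it through.** **Inputs from the protocol (section 2.9).** "considering a Cohen effect size of 0.40, a test power of 0.80, and a significance level of 5"%, read as Cohen's f = 0.40; three equal arms; "The sample is estimated to be of 39 patients with a potential addition of 20%, totaling 48 participants".

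**Assumptions, not in the document.** m = 6 on-treatment measures with variance 1 and common correlation ρ = 0.5; correlation r between baseline and each later score from 0.1 to 0.5; a constant treatment effect over T1 to T6; approximately normal scores.

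**Step 1: reproduce the planned figure.** The variance of a patient's on-treatment mean is V = [1 + (m − 1)ρ]/m = (1 + 5 × 0.5)/6 = 0.583. The noncentrality is λ = f²N/V = 0.16 × 39/0.583 = 10.70. With 2 and 36 degrees of freedom, power is 0.808, and N = 39 is the smallest total that reaches 0.80. Using m = 7 or 8 also gives 39 after rounding to equal arms; a one-way ANOVA with f = 0.40 would need 66. The 20% addition gives 39 × 1.2 = 46.8 or 39/0.8 = 48.75, so 48 is a fair rounding that divides by three.

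**Step 2: three ways of using P0.**

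- Covariate: variance V − r², degrees of freedom 2 and N − 4.
- Response level, change contrast (on-treatment mean minus P0): variance V + 1 − 2r, degrees of freedom 2 and N − 3.
- Response level, group main effect over seven visits: variance (7 + 30 × 0.5 + 12r)/49, with the effect diluted to 6/7, so λ is multiplied by 36/49; degrees of freedom 2 and N − 3.

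Power at N = 39 (0.808 if P0 is ignored):

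| r | Covariate | Change from P0 | Main effect with P0 |
|---|---|---|---|
| 0.1 | 0.815 | 0.429 | 0.766 |
| 0.3 | 0.871 | 0.571 | 0.721 |
| 0.5 | 0.968 | 0.808 | 0.680 |

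Power at N = 48 (0.891 if P0 is ignored):

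| r | Covariate | Change from P0 | Main effect with P0 |
|---|---|---|---|
| 0.1 | 0.896 | 0.520 | 0.857 |
| 0.3 | 0.937 | 0.675 | 0.819 |
| 0.5 | 0.990 | 0.891 | 0.782 |

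**Step 3: precision.** Covariate adjustment multiplies the variance by 0.98, 0.85 and 0.57 at r = 0.1, 0.3 and 0.5. At r = 0.5 confidence intervals narrow by 1 − √(0.333/0.583) = 24%. At r = 0 the cost is one degree of freedom: power at N = 39 is 0.807 against 0.808.

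**Step 4: bias or variance?** At 16 per arm the chance baseline difference between two arms has standard error √(2/16) = 0.35 SD. A null simulation of the unadjusted comparison (16 per arm, all correlations 0.5, 20,000 runs) gave a type I error of 0.052 and a mean arm difference of 0.003. Chance imbalance therefore adds variance and does not bias the result.

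**The case against.** The strongest reply is that section 2.13 names model families and lists no terms at all. A linear mixed model can carry a baseline covariate, potential confounders are collected, and a journal article commonly leaves the covariate list to the full protocol or analysis plan. This stands. A reader might infer that the trial's analyses are unadjusted, but the document does not say so.

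A reader might also infer that chance baseline imbalance must remain in the ginger effect. That does not follow. If P0 is a response level and the test is a group-by-time contrast from P0, stable patient differences and baseline imbalance are removed. At r = 0.5 this contrast has variance 0.583 + 1 − 1 = 0.583, the same as ignoring P0. At lower r it is clearly worse than ignoring P0, and it is less precise than the covariate model at every r examined.

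Three further limits hold.

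- No shortfall against "a test power of 0.80" is shown when P0 is simply left out: power is 0.808 at 39 and 0.891 at 48.
- The primary outcome is a short ordinal grade that may be near 0 before the first cisplatin dose. The gain there may be about one point or less, and the normal-theory figures are only a guide.
- The binary outcome is nausea in the 24 hours after an infusion, which has no direct counterpart before the first infusion. There is no case here for a baseline term in the logistic model.

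What remains is that the stated combination of time points and model invites the less efficient use of P0, and one sentence would prevent it.

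**Conclusion.** The point holds as a low-cost improvement in precision, not as a demonstrated error. The protocol lists P0 for evaluation and names a repeated measures ANOVA without saying how P0 enters. Across baseline correlations of 0.1 to 0.5, P0 as a covariate gave more power than either use of it as a response level. At N = 39 it moves power from 0.81 to between 0.815 and 0.97, whereas the group main effect with P0 in the response falls below the planned 0.80 throughout that range.

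These sizes rest on an assumed within-patient correlation of 0.5, an assumed baseline correlation, a constant on-treatment effect and near-normal scores. Expect the low end for CTCAE nausea and vomiting if grades before cisplatin are near 0, and more for QLQ-C30 and QLQ-CX24. Table 1 omits T0 for every outcome while section 2.6.1 lists P0, so it is not certain that a baseline score exists for each outcome. That conflict must be settled first.

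**What to change.** 1. In section 2.13, state that post-baseline scores will be analysed with a linear mixed model with fixed effects for group, visit, group-by-visit and the participant's own P0 score, and a random participant effect, and that P0 is a covariate and not a level of the response. Apply this to the CTCAE grades and to each QLQ-C30 and QLQ-CX24 scale with its own baseline score.
2. State whether the 15-day follow-up (P7) is part of the response.
3. Reconcile Table 1 (T1 to T6) with section 2.6.1 (P0 to P7), so that a baseline score is confirmed for each outcome.
4. Leave the logistic model for nausea after infusion as it is on this point.

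The cost is a few sentences and one degree of freedom per model, with no extra patients. If the CTCAE and quality-of-life measures are already taken at T0, there is no extra data collection; if not, they must be added to that existing visit. A rule is also needed for a missing baseline score, such as simple imputation, so that the participant stays in the intention-to-treat analysis.

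### Two unranked primary symptoms and a second nausea model are all judged at P<.05 with no decisive test, so the overall false-positive rate exceeds the single 5% used for sample size

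*Protocol article*

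**What the plan says.** - **Primary outcome (section 2.6.1):** "The primary outcome includes controlling nausea and vomiting as evaluated using the Common Terminology Criteria for Adverse Events". Nausea has grades 1 to 3 and vomiting grades 1 to 5. No composite is formed and neither symptom comes first. Table 1 lists CTCAE at T1 to T6.
- **Arms (sections 2.4 and 2.9):** two ginger doses and one placebo, "which will be equally allocated (1:1:1) into 3 groups of 16 patients each". The two dose-versus-placebo contrasts share a control group.
- **Analysis (section 2.13):** "For the analysis of quantitative data, repeated measures ANOVA based on the linear mixed effects model will be used". In addition, "A binary variable will also be created to indicate the occurrence of nausea in the 24 hours after the infusion" in at least one of the six weeks; for it a logistic model is fitted and "the odds ratio of occurrence of nausea will be calculated for the 3 groups". This second variable exists for nausea only.
- **Decision rule (section 2.13):** "Statistical significance will be set at" P<.05, with no distinction between analyses.
- **Sample size (section 2.9):** "considering a Cohen effect size of 0.40, a test power of 0.80, and a significance level of 5" per cent; "The sample is estimated to be of 39 patients with a potential addition of 20%, totaling 48 participants".

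**The concern.** The sample size is built for one test, but sections 2.6.1 and 2.13 open several routes to a positive trial: nausea grade, vomiting grade, any nausea after infusion, and for each of these a lower and a higher dose. The only endpoint that section 2.13 defines explicitly, any nausea within 24 hours, does not appear in section 2.6.1, so its standing is unclear. With 16 patients per arm, one nominal P<.05 on one symptom, dose or model could be reported as efficacy. The 5% in section 2.9 would then not be the error rate of that conclusion. What is at stake is whether a reader can tell beforehand which result decides the trial.

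**Working it through.** **1. Reproducing the plan's own figure.** Inputs from section 2.9 and Table 1: Cohen effect size 0.40 (read as f), power 0.80, alpha 0.05, k = 3 groups, m = 6 measurements. The article gives no within-patient correlation; rho = 0.5 is assumed.

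For the between-group test in a repeated-measures ANOVA, lambda = N·f²·m / [1 + (m − 1)·rho], with 2 and N − 3 degrees of freedom.

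- N = 39: lambda = 39 × 0.16 × 6 / 3.5 = 10.70, power 0.808. The stated 39 is reproduced.
- A plain one-way ANOVA would need 66, so that was not the formula used.
- The 20% addition: 39 × 1.2 = 46.8 and 39 / 0.8 = 48.75. The stated 48 lies between them.

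The stated size therefore matches one three-group test at 5%.

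**2. Counting the tests.** Two doses × (nausea mixed model, vomiting mixed model, nausea logistic model) = 6 dose-versus-placebo tests. Without the logistic model there are 4. If only three-group tests count, there are 2, or 3 with the logistic model.

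**3. Independent tests as a reference.** 1 − 0.95^c:
- c = 2: 9.75%
- c = 3: 14.3%
- c = 4: 18.5%
- c = 6: 26.5%

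**4. Correlated tests under no effect.** Two kinds of simulation were used. One draws normal test statistics, with correlation 0.5 between doses (shared control), 0.3–0.7 between symptoms and 0.5–0.8 between the two nausea analyses. The other draws patients: 16 per arm, within-patient correlation 0.5, the same symptom correlations, and a range of any-nausea rates. All the correlations other than the shared control, and the any-nausea rates, are assumptions.

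| What counts as a positive result | Any false positive, either direction | In favour of ginger (two-sided P<.05) |
|---|---|---|
| Two symptoms' three-group tests | 8–9% (9.75% if independent) | not directional |
| Four contrasts, gated by them | 7–8% | about 4% |
| Three three-group tests, logistic included | 11–14% | not directional |
| Six contrasts, gated | 9–11% | 5–6% |
| Four ungated contrasts | 15–17% | 7–9% |
| Six ungated contrasts, normal statistics | 19–24% | 10–12% |
| Six ungated contrasts, patient level, any-nausea rate 50% | 19–22% | up to about 11% |
| Six ungated contrasts, patient level, any-nausea rate 85% or more | 15–17% | from about 7% |

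At high any-nausea rates the logistic contrasts add almost nothing to the four ANOVA contrasts, because nearly every patient is a case.

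**5. Cost of splitting alpha over two symptoms.** Same formula at alpha = 0.025:
- N = 48: lambda = 48 × 0.16 × 6 / 3.5 = 13.17, power 0.82.
- N = 39: lambda = 10.70, power 0.71.

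**The case against.** Four points can be made on the other side.

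*A three-group analysis is named.* Section 2.13 describes no dose contrasts for the ANOVA, and the sample size reproduces as a three-group test. This stands. A reader might infer that any of six contrasts may be declared positive, but the article never says that the contrasts are ungated. On the gated reading the excess over 5% is modest.

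*The error in favour of ginger is smaller.* A reader might infer a chance of about 20% of a false claim for ginger. The documents do not support that. Figures near 20% count results in both directions, and one-sided testing is not stated. In favour of ginger, the ungated figures are about 7–12%, against 2.5% for a single two-sided 5% test. Nor does two symptoms × two doses × two analyses give eight tests, since the binary variable covers nausea only.

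*Multiplicity handling may sit in an analysis plan that is not shown.* This also stands, so the absence of an adjustment method is not the finding. The finding is what the article does state: an unranked two-symptom primary outcome, a second nausea model of unstated status, and one flat threshold.

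*Ranking the symptoms alters a registered trial.* Section 2.2 says recruitment is ongoing, and the trial is registered and ethics-approved. Choosing which symptom leads belongs to the investigators. For this reason the fix includes an option that keeps both.

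**Conclusion.** The point holds. Under the rule as written, the chance of at least one false-positive result in either direction is above 5% on every reading examined, while the sample size assumes one 5% test. The size depends on choices the article leaves open: roughly 7–9% on the most favourable reading, about 15–17% for four ungated contrasts, and 15–24% for six. The chance of a false result favouring ginger is about half of this. These figures rest on assumed correlations and an assumed any-nausea rate. They are a range and should not be quoted as a single number.

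**What to change.** In section 2.13:

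1. Make the three-group (2-df) repeated-measures test over T1–T6 decisive for the primary outcome.
2. Read each ginger-versus-placebo contrast only if that symptom's three-group test is significant, and at the same level as that test. With three groups this closed procedure holds the error within one symptom at that level.
3. Label the any-nausea odds ratio and the quality-of-life scales as supportive, with confidence intervals.
4. Across the two symptoms, choose one of the following:
   - **(a) Keep both as primary.** Test each three-group hypothesis at 2.5% and its contrasts at 2.5%; 2.5% + 2.5% keeps the total at 5%. State the power per symptom: about 0.82 with 48 patients and 0.71 with 39, under section 2.9's inputs and an assumed within-patient correlation of 0.5.
   - **(b) Order them.** The investigators name one symptom first, at 5%. The other is tested at 5% only if the first symptom's three-group test and both its dose contrasts are significant. Opening the second symptom on the three-group test alone would not hold 5%: if one dose truly affects the first symptom while the other dose and the second symptom are null, the error was 9–10% in simulation.

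The text change is a few sentences. The cost is that the logistic result, and under (b) the second symptom, can no longer carry an efficacy claim alone. Option (b) also changes the status of a registered primary symptom, so the registration and ethics record would need to follow. Option (a) avoids this but has less power if losses reach the 20% allowed for.

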### Patient and public involvement

2.14

All the patient information will be anonymously analyzed and processed. The results of our trial will be disseminated to the participating patients through a letter after publication.

## Discussion

3

This protocol entails a randomized trial that will determine the effects of antiemetic therapy associated or isolated with ginger on CINV is described. The strengths of this research include a triple-blind study method, which avoids ethical deviations and placebo-controlled randomization, and the ability to evaluate several simultaneous clinical outcomes. The limitations include the lack of adherence to the use of the proposed drugs, and lack of follow-up after the treatment. Subsequently, reduction of neutrophils beyond the minimum limit (neutropenia), although not a factor disconnection from the search, will delay the progress of the search and changes to the chemotherapy protocol may be required to ensure project completion.

Few studies with the same methodological design show positive results associated with the use of ginger. A randomized clinical study revealed that ginger supplementation at doses 0.5 g and 1.0 g significantly relieves the severity of acute nausea (within 24 hours).^[27]^ In addition, it delays CINV when associated with ondansetron and dexamethasone in a chemotherapy regimen with high emetogenic power.^[17]^

However, an experimental study that compared the effectiveness of ginger and chamomile in the management of cancer treatment induced gastrointestinal effects revealed that both herbal medicines reduce the frequency of vomiting with no significant difference between the 2 groups; however, ginger offered a notable reduction in the frequency of nausea.^[28,29]^ Furthermore, a clinical trial revealed that ginger can not only control nausea and vomiting, but can also enhance the quality of life of chemotherapy patients by reducing fatigue by up to 80%.^[30,31]^

## Ethics and dissemination

4

All procedures performed in this study involving human subjects will be conducted following the ethical standards of the 1964 Declaration of Helsinki and its subsequent amendments, the Madrid Declaration of the World Psychiatric Association, and the requirements established for manuscripts submitted to biomedical journals or ethical standards of good practice clinics. This trial was approved by the Human Research Ethics Committee of the North Riograndense Against Cancer, under the number CAAE 40602320.0.0000.5293 (approval date: February 3, 2021) and was registered in the Brazilian Registry of Clinical Trials under the number RBR-47yx6p9. Before registration of the trial participants, data confidentiality will be guaranteed through data anonymization.
